#### Recruitment {15}

Recruitment will take place in four mental health centres for traumatized children in the Netherlands: Child and Youth Trauma Centre Kenter Jeugdhulp, Arq, UMC Utrecht, and GGZ Rivierduinen. Children and their parents are informed about the study by their therapists and will receive written information. After their permission, contact details of potential participants are provided to the researchers, who will contact the children and parents separately to provide more details about participation in the study. Children and their parents who are eligible for the trial are asked for informed consent. To reach the targeted sample size, brochures about the study are handed out to referrers and are available for families and therapists at sites.

## Assignment of interventions: allocation

### Sequence generation {16a}

Random allocation to either condition is needed, in order to reduce selection bias and to be able to attribute effects to parenting training and family sessions added upon an intensive trauma therapy. After informed consent is provided, families will be randomly assigned within each site to one of the treatment conditions. Within the multicentre trial, families are randomized by an independent researcher, following a computer-generated list with each participant having a 33.3% chance of being assigned to FITT, ITT, or TAU. The results of the randomization are communicated to the site per participating family.

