## Methods: participants, interventions, and outcomes

### Study setting {9}

This multicentre research study takes place in four different clinical health care settings for youth in the Netherlands: Child and Youth Trauma Centre Kenter Jeugdhulp, GGZ Rivierduinen, UMC Utrecht, and Arq.

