#### Sample size {14}

Power analysis was conducted to determine whether an informative trial could be conducted given limitations imposed upon the maximum sample due to the duration of the study and size of the population of children indicated for trauma treatment, using G*power 3 [95]. Sample size calculation was made based on the assumptions of the primary objective and the first secondary objective. A priori, we decided that adding systemic intervention elements to individual trauma therapy would be justified if it would mean that on average at least one out of five children would have clinically significant benefit when given the full FITT compared to treatment without systemic elements (number needed to treat = 5; equivalent to *f* = 0.18).

For primary objective 1 (Does intensive trauma therapy with a family-based component (FITT) lead to a stronger reduction of trauma symptoms and stronger increase of structural emotional safety than intensive trauma therapy without this family-based component (ITT)?), the sample size was calculated based on between 2 groups by within effect with at least two measurements (pre, end/follow-up), setting *f* = 0.18 with a power of 80% and a significance level of 5% (two-sided). Default settings were used for the correlation among repeated measures (= 0.5) and non-sphericity correction (*ε* = 1). According to the power analysis, a total sample size of 64 children is required.

Secondary objective 1 (Does intensive trauma therapy with a family-based component (FITT) lead to faster reduction of trauma symptoms and increase of structural emotional safety than low-frequency trauma treatment with parent therapy and family sessions?) is based on two measurements (pre and intermediate/follow-up). In accordance with the first sample size calculation, we tested with setting *f* = 0.18 with a power of 80%, a significance level of 5% (two-sided) was used. Again, default settings were used for correlation among repeated measures (= 0.5) and non-sphericity correction (*ε* = 1). Based on this calculation, a total sample size of 64 children is required.

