## Statistical methods

### Statistical methods for primary and secondary outcomes {20a}

The measurement level of each variable is at least ordinal. We control for the duration and severity of family violence [96], child functioning, parental psychopathology [97], and new incidents of family violence as a priori potential confounders. Analyses will be performed using the latest version of the software package Statistical Package for the Social Sciences (SPSS). First, to determine whether changes on continuous measures are different per treatment, we use linear mixed models. Continuous measures with only one time point will be analysed with independent samples *T*-test. Changes in categorical outcomes over the course of treatment across the conditions are tested with generalized estimating equations (GEE). To handle missing data, we will use maximum likelihood estimation within the linear mixed model analyses. For the planned GEE, we will explore the possibilities to deal with missing data, depending on the amount, randomness, and type of data missing. Analyses will primarily be performed according to the principles of intention-to-treat; however, they will be repeated as per-protocol analyses (see Table 4).

**Table 4 Tab4:** Statistical analyses

*Statistical analyses*					
	Measure	Type of data	Timepoints	Statistical analysis	Subjects
Child PTSD	CAPS-CA	Categorical	3	GEE	ITT/PP
	CRIES	Continuous	4	Mixed models	ITT/PP
	TSCC	Continuous	3	Mixed models	ITT/PP
Child functioning	SDQ	Continuous	3	Mixed models	ITT/PP
	CDI	Continuous	3	Mixed models	ITT/PP
	CDC	Continuous	3	Mixed models	ITT/PP
Parent functioning	NOSI-K	Continuous	4	Mixed models	ITT/PP
	Trauma-informed	Continuous	3	Mixed models	ITT/PP
	TSI	Continuous	3	Mixed models	ITT/PP
	YAS-R	Continuous	3	Mixed models	ITT/PP
	DPAS	Continuous	3	Mixed models	ITT/PP
Structural emotional and physical safety	CTS	Continuous	3	Mixed models	ITT/PP
	CTS-pc	Continuous	3	Mixed models	ITT/PP
	PRTI	Continuous	3	Mixed models	ITT/PP
	ACE-Q	Continuous	3	Mixed models	ITT/PP
	New IPV incidents	Continuous	4	Mixed models	ITT/PP
	SIS	Continuous	3	Mixed models	ITT/PP
	SIFS	Continuous	3	Mixed models	ITT/PP
	SIM-PR	Continuous	3	Mixed models	ITT/PP
	Security scales	Continuous	3	Mixed models	ITT/PP
	FIT	Categorical	1	Independent samples T-test	ITT/PP

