Descriptive and exploratory analyses will be carried out by standard methods. All continuous scores will be examined for normality. If variable distributions deviate too much from normality, corrective steps will be taken either by transforming variables or by using non-parametric tests. We will control for child functioning, parental psychopathology, duration, severity, and intensity of interparental violence, and new IPV incidents. The variables are treated as covariables in the analyses mentioned below.

To examine our primary hypothesis, linear mixed models will be used in case of continuous data. GEE will be used for the categorical data. We will use the end of treatment (T12/T14) and intermediate/follow-up time-point (T13) to compare FITT with ITT (objective 1).

To examine our secondary hypotheses, linear mixed models will be used. We will use the end of treatment time-point (T12/T14) to compare FITT with TAU. Control measures are child functioning; parental psychopathology; duration, severity, and intensity of interparental violence; and new IPV incidents. The variables are treated as covariables in the up-mentioned analyses. We will use the Benjamini-Hochberg method to correct for multiple comparisons.

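### Families are randomised within each of four sites, but the enumerated covariates and the models contain no site term; the cost is in efficiency and calibration, not bias

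*Protocol article*

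**What the plan says.** Study setting {9} places the trial in "four different clinical health care settings for youth in the Netherlands". Sequence generation {16a} states that "families will be randomly assigned within each site to one of the treatment conditions", "following a computer-generated list with each participant having a 33.3% chance of being assigned to FITT, ITT, or TAU". Neither that section nor Concealment mechanism {16b} mentions blocks or equal numbers per arm within a site. The consent section {26a} describes the procedure as a computerised lottery.

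Statistical methods {20a} lists the adjustment variables three times:
- "We control for the duration and severity of family violence [96], child functioning, parental psychopathology [97], and new incidents of family violence"
- "We will control for child functioning, parental psychopathology, duration, severity, and intensity of interparental violence, and new IPV incidents"
- "Control measures are child functioning; parental psychopathology; duration, severity, and intensity of interparental violence; and new IPV incidents"

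Site is in none of these lists. On the model, the section says "To examine our primary hypothesis, linear mixed models will be used in case of continuous data", with GEE for categorical outcomes. Neither {20a} nor {20c} names a site fixed effect, random effect or clustering term.

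**The concern.** Where allocation is made separately within sites, site is part of the design, and the usual practice is to carry it into the analysis. Here the adjustment set is enumerated and repeated, yet the one variable that the randomisation itself uses is missing.

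Two things are at stake. If allocation is balanced within site, an analysis without site leaves between-site variance in the error term although the design has removed it from the treatment contrast. Intervals are then too wide and the test is conservative. If allocation is not balanced within site, chance differences in the site mix of the arms stay unadjusted. The trial is powered at about 81% for its primary comparison, so there is little slack.

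**Working it through.** **1. The plan's own figure.** Inputs from Sample size {14}: f = 0.18, two groups, two measurements (m = 2), correlation ρ = 0.5, ε = 1, two-sided α = 0.05. For the group-by-time effect:

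λ = f² · N · m / (1 − ρ) = 0.0324 × 64 × 2 / 0.5 = 8.29, with df = (1, 62).

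The noncentral F gives power 0.809, and N = 64 is the smallest even total that reaches 80%. With 32 per arm and three arms, 96 / 0.8 = 120. Both stated figures reproduce, and neither allows for site.

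**2. The same effect as a change score.** d = 2 · √(f² · m / (1 − ρ)) = 2 · √0.1296 = 0.72 SD of change, with 32 per arm.

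**3. With and without site.** Simulation of 20,000 trials per setting, N = 64, four equal sites, site as a fixed factor in the change-score model. The share of change-score variance due to site is an assumption. Type I error is for the analysis that omits site.

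Balanced allocation within site:

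| Site share | SE ratio, omitted / included | Type I error, omitted | Power, omitted | Power, included |
|---|---|---|---|---|
| 0% | 1.000 | 0.046 | 0.809 | 0.809 |
| 2% | 1.011 | 0.047 | 0.816 | 0.819 |
| 5% | 1.027 | 0.046 | 0.811 | 0.824 |
| 10% | 1.057 | 0.037 | 0.817 | 0.844 |
| 20% | 1.122 | 0.030 | 0.829 | 0.885 |

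Simple draw within site:

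| Site share | Type I error, omitted | Power, omitted | Power, included |
|---|---|---|---|
| 0% | 0.051 | 0.801 | 0.780 |
| 2% | 0.048 | 0.804 | 0.791 |
| 5% | 0.052 | 0.807 | 0.806 |
| 10% | 0.052 | 0.802 | 0.821 |
| 20% | 0.049 | 0.801 | 0.867 |

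A second simulation of the simple draw (8,000 runs) gave equal power, 0.80 and 0.80, at a 3% share. Break-even is therefore near 3–5%.

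**4. Chance imbalance under a simple draw.** Assume 64 / 4 = 16 FITT and ITT children per site. The probability that a given site splits 11:5 or worse is 2 × P(X ≤ 5) for X ~ Binomial(16, 0.5), which is 0.21.

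**5. Which site term matters.** With complete data at two times, the group-by-time estimate is the difference between arms in mean change. A site main effect shifts a child's scores equally at both times and drops out of the change. In one simulated complete data set (64 children, four sites, balanced arms, site differences in both level and change), the standard error of group-by-time was 0.2525 without site, 0.2525 with a site main effect, and lower, at 0.2347, only once site-by-time terms were added.

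**The case against.** The other side has four arguments.

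- **The document does not state balance within site.** It describes a one-in-three chance and a lottery, with no blocks. A reader might infer from allocation within sites that standard errors are certainly too large, but that needs enforced balance. Under a simple draw the test without site holds its level, and adding site can cost a little power. This stands, and it is why both cases are shown.
- **Site differences are not documented.** A reader might infer that each site delivers its own usual care. The section on TAU components says the opposite: it calls TAU comparable across the four centres. Training and supervision in the intensive programmes are also shared. This stands as far as it goes. The same section still allows individual or group format, several processing methods and family work only on indication, so differences in change remain possible, but their size is unknown.
- **The list may cover confounders only.** {20a} introduces its variables as potential confounders, and a condensed article may leave design terms to an analysis plan. Nothing says that site will be excluded. This tempers the point without removing it: the article enumerates and repeats an adjustment set, and a site term added after the data are seen would depart from it.
- **Site in every model is not free.** With 64 children, four sites and two arms there are about 8 per cell (64 / 8), which is thin for CAPS-CA diagnostic status in a GEE. This stands and limits the fix.

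**Conclusion.** The point holds as a modest one about efficiency and calibration. Allocation is within site, and the published adjustment set and models have no site term. A reader might infer that the treatment effect is biased; it is not, because allocation is random within every site in either case.

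The size depends on two things that the document does not settle: whether arms are balanced within site, and how much of the variance in change is due to site. With balance and an assumed 2–10% site share, standard errors are about 1–6% too large and about 0–3 power points are lost. With a simple draw, type I error is near 5%. Adding site then ranges from a loss of about 2 points at 0% to a gain of about 2 points at 10%, with break-even near 3–5%. The 20% row shows how the effect grows, but nothing in the document supports a share that high. All figures assume equal site sizes and complete data.

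A reader might also infer that a site main effect would recover the lost precision. For the group-by-time effect that the trial is powered on, it would not. Confidence is high that site is missing and moderate on how much it matters.

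**What to change.** Before the data are seen, state in the analysis plan:

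1. Site enters as a fixed factor. In the repeated-measures mixed models it is accompanied by site-by-time terms. Alternatively, use a baseline-adjusted or change-score model with site as a fixed factor.
2. Site enters the GEE where cell counts allow, with the rule for leaving it out fixed in advance.
3. Whether the within-site lists are blocked, since this decides which of the two cases applies.

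Site is known for every family because allocation is made within it, so no new data are needed. The cost is about 3 degrees of freedom for a given change contrast (62 to 59 in the two-arm comparison) and at most 1–2 power points if site differences are negligible.

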### Concealment mechanism {16b}

Participating families are randomized by an independent researcher, following a computer-generated list with each participant having a 33.3% chance of being assigned to FITT, ITT, or TAU. The results of the randomization are provided to the centre per participating family. Subsequently, the measures and intervention will start.

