The Security Scale [71, 72] is a 15-item self-report questionnaire for children between the ages of 8 and 18 and measures self-reported attachment security with their parents [73]. Children and parents (independently) report on responsiveness and availability of the parent in the parent-child relationship (attachment). Each item is rated on a 5-point Likert scale (1 = strongly agree, 5 = strongly disagree). An example item is *I feel my mother really understands me*. Several studies indicate adequate reliability and validity [74]. High internal consistencies for 10 and 12-year-olds (*α* = 0.82, *α* = 0.79) are reported [75]. Test-retest reliability over a 2-week period was high (*r* = 0.75) [73]. The Security Scale is related to other attachment measures [75]. In a Dutch sample, internal consistency for the child version was *α* = 0.81 [76].

The Family Interaction Task (FIT) [77] is an observational instrument that measures parent-child interaction and consists of four tasks in which parent and child are instructed to complete a series of interactive tasks together. The FIT consists of four structured tasks: (1) guessing words by getting clues, (2) etch a sketch, (3) conflict task, and (4) completing a difficult but solvable puzzle by untangling a fixed ring from a standard within 4 min. These tasks are designed to elicit variations in parental and adolescent autonomy-promoting behaviours and emotional affect. The tasks are originally developed for children in middle childhood, but the tasks have been adapted for adolescents. Rating scales range from 1 to 5 and a higher score indicates a greater presence of that particular construct. Ratings are based on the complete session. Each videotaped session is independently coded by two coders (researchers). Interrater reliability was adequate (*n* = 101, ICC range .87–.94) in a Dutch sample [76].

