### Implementation {16c}

An independent researcher will generate the allocation and directly informs the treatment team by e-mail about the treatment arm that families receive according to the randomization list. The therapist informs the families.

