## Assignment of interventions: blinding

### Who will be blinded {17a}

Until randomization, both families and therapists are blind to the treatment allocation to mitigate bias due to expectation or disappointment. Nobody will be blinded during the intervention.

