### Procedure for unblinding if needed {17b}

The design is open-label, and only data analysts will be blinded. Unblinding will therefore not occur.

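### The written order lets T0 be collected after the arm is known, and no masking is planned for the researchers who conduct CAPS-CA and code the FIT videos

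*Protocol article*

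**What the plan says.** **Order of events.** The consent section (26a) and Sequence generation {16a} place only eligibility and informed consent before randomisation. Concealment mechanism {16b} says that the result goes to the centre for each family, and then: "Subsequently, the measures and intervention will start". Under Implementation {16c}, the independent researcher "directly informs the treatment team by e-mail about the treatment arm that families receive according to the randomization list". The same section adds: "The therapist informs the families". It does not say when this happens relative to T0.

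**Blinding.** Who will be blinded {17a} keeps families and therapists blind until randomisation, to reduce bias from expectation or disappointment, and continues: "Nobody will be blinded during the intervention". Procedure for unblinding {17b} states: "The design is open-label, and only data analysts will be blinded".

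**Who rates.** Under Plans for assessment {18a}, trained and certified researchers conduct and score CAPS-CA. FIT sessions are videotaped and coded independently by two researchers. Both instruments stand under Primary outcomes. In Table 3, CAPS-CA is taken at T0 and T13, and FIT at end of treatment only. Every other measure in the two primary domains is a child or parent questionnaire.

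**The concern.** There are two separate weaknesses.

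**Baseline.** The trial is sized on pre-post change, and the mixed models test whether change differs by arm. If a family knows its arm when it completes T0, any shift in reporting caused by that knowledge enters the estimated effect. Child functioning and parental psychopathology are model covariates. If their values come from a T0 completed after disclosure, the adjustment uses variables that the allocation may already have touched. A family that withdraws on hearing its arm, before T0, has no baseline.

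**Raters.** The article's background section names informant bias in self-report as a weakness of this field and calls for interview and observation measures as well. CAPS-CA and FIT meet that call. Much of their advantage is lost if the rater knows the arm. FIT is the more exposed: it is measured once and compared with a t-test, so no baseline can absorb a rating bias.

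Rater bias can affect both FITT versus ITT and FITT versus TAU. Expectation bias at baseline is most plausible for FITT versus TAU, where one arm is intensive and the other is usual care. It remains possible for FITT versus ITT, because only FITT brings in the family.

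**Working it through.** **The text, side by side**

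| Question | What the article fixes | What it leaves open |
|---|---|---|
| What comes before randomisation? | Eligibility (intake interview, standardised questionnaires) and consent | Whether any T0 measure is among the intake questionnaires |
| When do the measures start? | After the centre has the result | Whether all T0 measures are meant |
| Who is sent the arm? | The treatment team; families through the therapist | When families hear, relative to T0 |
| Who is blinded after randomisation? | Data analysts only | Whether interviewers and coders in fact learn the arm |

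Nothing places T0 before disclosure, and nothing provides for masked interviewers or coders.

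**Arithmetic, to give a scale**

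Inputs from Sample size {14}: f = 0.18, two groups, m = 2 measurements, correlation ρ = 0.5, ε = 1, two-sided 5%, 80% power, total N = 64, with 20% added for loss. Trial design {8} gives 96 completers. The bias b is an assumption: 0.1 to 0.2 SD.

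1. *The plan's own figure.* For the group-by-time interaction, λ = f² × N × m / (1 − ρ) = 0.0324 × 64 × 2 / 0.5 = 8.29, with 1 and 62 degrees of freedom. Power is 80.9%. N = 62 gives 79.6%, so 64 is the smallest even total that reaches 80%. Then 3 × 32 = 96 and 96 / 0.8 = 120. Both figures reproduce.
2. *Difference in change implied by f = 0.18.* SD of change = √(2(1 − ρ)) = 1 SD. With n = 32 per arm, λ = δ² × n / 2 = 16δ², so δ = √(8.29 / 16) = 0.72 SD.
3. *False-positive rate under no true effect.* A spurious difference b in change gives a t-test noncentrality of b / √(2/32) = b / 0.25. For b = 0.1 this is 0.4, and the nominal 5% becomes 6.8%. For b = 0.2 it is 0.8, and the rate is 12.4%.
4. *Relative size.* 0.1 / 0.72 = 14% and 0.2 / 0.72 = 28%.

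Step 3 applies to continuous scores analysed as change. It does not carry over directly to CAPS-CA, which Table 4 analyses as categorical by GEE. FIT has no change score, but a t-test on a single score with SD 1 and 32 per arm has the same noncentrality, so a rating bias of 0.1 to 0.2 SD would give the same rates.

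**The case against.** Several points on the other side stand, and they set the limits of this one.

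- A reader might infer that T0 is always taken with the family knowing its arm. The article does not say so. The order of measures and the informing of families appear in separate sections, and the second has no timing. Some eligibility questionnaires precede randomisation, and the participant-flow figure is not available in the text reviewed. What can be said is that the written order permits it.
- A reader might infer that the raters are told the arm. No section says this; the e-mail goes to the treatment team. What is missing is any provision that keeps the arm from them, and the blinding statement is confined to analysts.
- A reader might carry the contrast between intensive and usual treatment over to the primary comparison. FITT and ITT are both intensive, so that mechanism belongs mainly to the secondary comparison with TAU.
- A reader might set the assumed shift against 2f = 0.36 SD and arrive at a larger share. The article gives no such target, and the calculation that yields N = 64 corresponds to 0.72 SD in change.
- Rater training, certification, double coding and inter-rater checks limit scoring latitude. They do not remove a bias shared by raters who know the arm, because such raters can agree with one another.
- Masking raters does nothing for the many questionnaires in an open-label therapy trial. That is true, and it is why the two rated outcomes are worth protecting.

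**Conclusion.** The point holds in this form: the plan as written protects neither T0 nor the two researcher-rated primary-domain outcomes from knowledge of allocation. For T0, the order allows the exposure but does not establish that it occurs; this limb covers CAPS-CA and the questionnaires, not FIT. For the raters, the absence of planned masking follows from the article's own statement that blinding is confined to analysts.

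The documents give neither the size nor the direction of any bias. The rise in the false-positive rate to about 7% to 12% rests on an assumed 0.1 to 0.2 SD, 32 per arm, ρ = 0.5 and no true effect. It shows scale and is not an estimate. The recommendation does not depend on it, because the remedy is cheap and leaves the sample size, measures and treatments unchanged.

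**What to change.** 1. In {16b} and {16c}, state that all T0 measures are completed after consent and before the independent researcher releases the allocation. If that is already the practice, the wording still needs correcting.
2. For families already enrolled (recruitment began in March 2021), record whether T0 came before or after the family learned its arm, and run a sensitivity analysis on that basis.
3. In {17a}, {17b} and {18a}, state that CAPS-CA interviewers are not told the arm and that families are asked not to reveal it.
4. In the same sections, state that FIT videos are coded under a study ID without the arm. Stored recordings from families already enrolled can be coded, or recoded, in the same way.

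The cost is a short delay before the allocation is released, plus relabelling of files; no new staff or measures are needed. Some accidental unblinding will remain, above all in the CAPS-CA interview, where the child may mention the treatment received.
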